### Resource Use and Costing

#### BNBD-NDD Cost

The direct cost of BNBD-NDD to the families is primarily the retail cost of the intervention. As the program was offered free of charge for our RCT, we used the average of parents’ (proxy payers for their children) reported willingness to pay. The participating families were expected to have internet access, which was not assessed or included in the direct costs. Retail pricing will be explored further from the willingness to pay data, which obtained a hypothetical willingness to pay (HWTP) by directly asking for the maximum cost participants would pay for the program. The HWTP responses may contain hypothetical bias influenced by factors such as the absence of a budget constraint effect and strategic answering, as some may perceive their input to potentially affect future pricing [37].

#### Treatment Utilization

The TU questionnaire [38] estimated the health care services families sought to address their children’s sleep problems, including publicly and privately funded ones. Care may be provided by family physicians, physician specialists (eg, pediatricians), and other health professionals (eg, psychologists). The mean frequency and costs of these services at baseline and at 8 months for the BNBD-NDD and usual care groups will be compared to see if BNBD-NDD impacted the usage rate. Out-of-pocket expenses reported for a health professional’s or provider’s help will also be assessed. Unit costs will be estimated using publicly available resources, such as the Canadian Agency for Drugs and Technologies in Health [39].

### Data Analysis

#### Overview

For the reference case CEA analysis, the mean sample PedsQL at baseline and 8 months will be compared. Regression analyses will examine the impacts of baseline characteristics (geographical region, age groups, sex, household income, and NDD diagnosis) on the efficacy measures. For all regression analyses, the mean difference between groups will be reported, as well as the variance, *P* value, and goodness of fit using *R*^2^.

#### Reference Case CEA

In the reference case analysis using the family payer perspective, the ratio of the difference in mean cost between groups to the difference in mean PedsQL total score per group will be used to estimate the ICER. An ICER will be calculated from the family’s perspective.

ICER = Costs_(BNBD-NDD + usual care)_ − Costs_(usual care)_ / Effect_(BNBD-NDD + usual care)_ − Effect_(usual care)_

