### Sample Size Calculation

The BNBD-NDD RCT was powered to detect a group by time interaction across the 3 data collection time points (baseline, 4-month, and 8-month) and between the BNBD-NDD and usual care groups. The primary sleep outcome was the Disorders of Initiating and Maintaining Sleep (DIMS) [22] variable. To achieve a power of 0.80 with an α of .05, 39 participants per group would have to complete the DIMS measure at 8 months. Based on this analysis and the anticipated postenrollment dropout rate of 50% from a previous BNBD RCT, an estimated 160 participants were targeted for enrollment at baseline.

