### Randomization and Blinding

Participants were randomized using a block stratified approach with 1:1 allocation to either the intervention (BNBD-NDD) or the usual care group and were not blinded to their assigned group. Stratification was by parent-reported primary NDD diagnosis.

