### Outcomes for Economic Evaluation

PedsQL is an instrument that measures generic (rather than disease-specific) HRQoL and has been shown to have appropriate psychometric properties when used with children with NDDs [31]. It can be used to evaluate HRQoL in healthy children, youths, and those with medical conditions [32]. PedsQL uses a modular approach with 4 multidimensional scales on physical, emotional, social, and school functioning [33]. Parents rate each item using a 5-point Likert scale from 0 (never) to 4 (always) [31]. A Total Scale Score is calculated by adding all of the items and dividing the total by the number of items answered in all scales [33]. Mean Scale Scores are computed by dividing the sum of the items by the number of items answered in the scale [33]. Depending on the age of the participant's child, 3 parent-report versions were used (for ages 2-4 years, 5-7 years, and 8-12 years) to accommodate the age range of this study sample. The difference between the intervention and usual care groups’ average Total Scale Score in parent-proxy reports of their children’s PedsQL at baseline and 8 months will be evaluated in the reference case CEA. Secondary analyses will examine each of the 4 modules and age group trends; it is noted that inconsistent reporting of the school functioning section may occur due to age and the time of year of data collection (off-school period). The scoring and missing data (where applicable) will be completed in accordance with the PedsQL user manual [34].

In the CCA, the children’s sleep and parental outcomes are analyzed by comparing baseline and 8-month data and looking at changes in sample averages. Based on parent-reported questionnaire data, the DIMS score quantifies the severity of children's sleeping problems. The Single Item Fatigue Impact Scale [35] and the Depression, Anxiety, and Stress Scales [36] are used to evaluate the daytime fatigue and psychosocial health, respectively, of parents. Single Item Fatigue Impact Scale is adapted from the 40-item Fatigue Impact Scale [35]. The Depression, Anxiety, and Stress Scales have demonstrated adequate construct validity and high reliability [36].

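### The ICER is built from unadjusted differences in arm means although baseline PedsQL and service use are collected, so chance baseline imbalance enters the denominator and precision is lost

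*Protocol article*

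**What the plan says.** Under Reference Case CEA, the ICER is "the ratio of the difference in mean cost between groups to the difference in mean PedsQL total score per group", followed by a formula in plain arm costs and effects. No covariate appears in either.

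The effect is described in two other places. Outcomes for Economic Evaluation refers to the between-arm difference in "average Total Scale Score in parent-proxy reports of their children’s PedsQL at baseline and 8 months will be evaluated in the reference case CEA". The Data Analysis overview says that "the mean sample PedsQL at baseline and 8 months will be compared". Time Horizon likewise focuses on the baseline and 8-month data. None of these says whether the effect is the difference at 8 months or the difference in change from baseline.

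The same overview adds: "Regression analyses will examine the impacts of baseline characteristics (geographical region, age groups, sex, household income, and NDD diagnosis) on the efficacy measures". It says these regressions will report a mean difference between groups. Baseline PedsQL and baseline cost are not among the five characteristics, and nothing carries a regression estimate into the ICER.

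Both baselines exist. PedsQL is measured at baseline, and for service use Treatment Utilization says: "The mean frequency and costs of these services at baseline and at 8 months for the BNBD-NDD and usual care groups will be compared". On the design, Randomization and Blinding says: "Stratification was by parent-reported primary NDD diagnosis". No other stratification factor is given.

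**The concern.** The baseline value of a repeated scale is usually among the strongest predictors of its later value. Randomisation here balances diagnosis but does nothing specific to balance PedsQL. With few completers per arm, a visible chance difference in baseline PedsQL is to be expected. An ICER taken from raw arm means carries part of that difference in its denominator, where a small absolute error can move the ratio a good deal if the true difference is small. The information needed to remove it has already been collected.

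The open choice between 8-month means and change scores makes this worse. In any one dataset the two estimates differ by exactly the observed baseline difference, so the unsettled definition can itself alter the ICER.

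**Working it through.** **Completers per arm.** Sample Size Calculation states: "To achieve a power of 0.80 with an α of .05, 39 participants per group would have to complete the DIMS measure at 8 months". With the stated 50% dropout, 39 / (1 - 0.5) = 78 per arm, or 156 in total, against the stated target of 160. The two agree to within rounding up. Working back, 160 x 0.5 / 2 = 40 completers per arm, which is used below. The 39 was set for the sleep outcome (DIMS), so 40 is only the expected number available for PedsQL.

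**Assumptions.** PedsQL has the same SD at baseline and 8 months and in both arms; results are in units of that SD. The baseline to 8-month correlation r is not in the article. The main range is 0.5 to 0.7, with 0.3 shown as a low value.

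**Chance imbalance.** The standard error of the baseline difference is sqrt(2/40) = 0.224 SD.

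**Shift in the effect from a one-standard-error imbalance.**
- 8-month means: r x 0.224
- change scores: -(1 - r) x 0.224
- baseline-adjusted: 0 in expectation

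**Variance of the estimated difference.**
- 8-month means: 2/n
- change scores: 2(1 - r) x 2/n
- baseline-adjusted: (1 - r²) x 2/n

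Adjustment therefore reduces variance by r² against 8-month means. Against change scores, (1 - r²) / [2(1 - r)] = (1 + r)/2, a reduction of (1 - r)/2.

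| r (assumed) | Shift, 8-month means | Shift, change scores | Variance cut vs 8-month means | Variance cut vs change scores |
|---|---|---|---|---|
| 0.3 | +0.07 SD | -0.16 SD | 9% | 35% |
| 0.5 | +0.11 SD | -0.11 SD | 25% | 25% |
| 0.7 | +0.16 SD | -0.07 SD | 49% | 15% |

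**Gap between the two readings.** The 8-month difference minus the difference in change equals the baseline difference, so a one-standard-error imbalance separates them by 0.224 SD whatever r is.

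**Simulation check** (20,000 runs, 39 per arm, r = 0.3, 0.5, 0.7). The correlation between the estimated effect and the baseline imbalance was 0.30, 0.49 and 0.70 for 8-month means; -0.59, -0.51 and -0.39 for change scores; and about 0 after baseline adjustment. This agrees with the formulas.

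**The case against.** The strongest reply is that the outcome sections can be read as change from baseline, which does use baseline PedsQL. That reading is fair. It limits the loss when r is high: at r = 0.7 the shift is 0.07 SD in size and the variance gain 15%. It does not remove the problem, because a change score over-corrects and imbalance then enters with the opposite sign. Nor does Reference Case CEA say that change is meant.

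A second reply is that the article is condensed, that its formula is the generic ICER, and that covariates are often left to an analysis plan. The formula does not forbid adjusted means. But the article goes beyond silence: it describes the ICER in terms of group means and separately lists regression covariates for another purpose. The between-group difference from those regressions may include diagnosis, but it lacks baseline PedsQL and has no stated route to the ICER.

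A reader might infer several stronger things that the document does not support:
- *The ICER's components are biased by lack of adjustment.* Under randomisation, raw differences in means are unbiased on average. The fault is conditional imbalance and lost precision.
- *Adjustment is worth nearly doubling the sample.* 1/(1 - 0.49) = 1.96 holds only for 8-month means at r = 0.7. Against change scores at the same r it is 1/0.85 = 1.18.
- *The shift is a given share of the treatment effect.* The article states no expected PedsQL effect, so any such percentage depends on an invented denominator.
- *Ignoring the stratum makes standard errors too large.* That holds only if diagnosis predicts PedsQL or cost. No figure is given for this, and the section specifies no standard error for the ICER.

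**Conclusion.** The point holds as one of efficiency and of an unsettled estimator. The ICER as described makes no stated use of baseline adjustment, and under either reading of the effect an adjusted analysis is more precise and free of chance baseline imbalance for any r between 0 and 1. With 40 completers per arm and r of 0.5 to 0.7, a one-standard-error imbalance moves the denominator by 0.07 to 0.16 SD in size, with the sign depending on the reading. The variance forgone is 15% to 49%, again depending on the reading.

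These sizes rest on an assumed r, on equal SDs, and on a completer number planned for DIMS. Missing Data restricts the analysis to participants with both time points, and 50% dropout was expected, so selective attrition may add baseline differences that are not due to chance. Baseline adjustment would address those only in part. The sample size calculation is not in question. The change is worth making before the comparison is run.

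**What to change.** In Reference Case CEA, define the effect as the between-arm difference in 8-month PedsQL total score from a regression on arm, baseline PedsQL total score and NDD diagnosis stratum. Subgroup Analysis expects relatively few participants with CP or FASD, so those strata may be pooled. This also settles the choice between 8-month and change values.

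For incremental cost, adjust the service-use component for baseline treatment-utilization cost and stratum. The programme price should stay outside that adjustment: under BNBD-NDD Cost it is set from average willingness to pay, which baseline service use cannot help to estimate. Form the ICER from the adjusted differences. A net-benefit analysis is not part of this fix, since it would need a value per PedsQL point that the article does not give.

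The Results section says the economic data are cleaned and being prepared for analysis, so the change should be a dated amendment recording that the choice was made before the outcome comparison was run. The cost is that amendment and slightly more analysis work; no new data are needed.

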**Methods:**

The BNBD-NDD RCT evaluates the impacts of the intervention on children’s sleep and quality of life, as well as parents’ daytime functioning and psychosocial health. Parent participants were randomized to the BNBD-NDD treatment or to usual care. The economic evaluation assesses outcomes at baseline and 8 months later, which include the PedsQL as the primary measure. Quality of life outcomes facilitate the comparison of competing interventions across different populations and medical conditions. Cost items include the BNBD-NDD intervention and parent-reported usage of private and publicly funded resources for their children’s insomnia. The economic evaluation involves a reference case cost-effectiveness analysis to examine the incremental cost of BNBD-NDD per units gained in the PedsQL from the family payer perspective and a cost-consequence analysis from a societal perspective. These analyses will be conducted over an 8-month time horizon.

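### The PedsQL effect in the ICER is not tied to one time contrast and is not regression-adjusted for baseline PedsQL; one baseline-adjusted arm difference would be clearer and more precise at no data cost

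*Protocol article*

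**What the plan says.** All references are to the Protocol article; no SAP is shown.

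- **Reference Case CEA** gives the operative rule: "the difference in mean PedsQL total score per group will be used to estimate the ICER". The formula below it has a generic effect term for each arm. No time point or model is given there.
- **Outcomes for Economic Evaluation** describes a contrast between the arms, in which the "average Total Scale Score in parent-proxy reports of their children’s PedsQL at baseline and 8 months will be evaluated in the reference case CEA".
- **Data Analysis, Overview** says that "the mean sample PedsQL at baseline and 8 months will be compared" and names no arm contrast in that sentence.
- **Abstract, Methods** describes the target as the "incremental cost of BNBD-NDD per units gained in the PedsQL from the family payer perspective", which suggests change.
- **Time Horizon** says that the reference case draws mainly on the baseline and 8-month assessments.
- **Overview** also plans covariate work: "Regression analyses will examine the impacts of baseline characteristics (geographical region, age groups, sex, household income, and NDD diagnosis) on the efficacy measures". It promises that every regression will report a mean difference between groups. Baseline PedsQL is not in the list.
- **Randomization and Blinding** states: "Stratification was by parent-reported primary NDD diagnosis". Nothing in the design balances baseline PedsQL.
- **Sensitivity Analysis** varies costs and service use, not the definition of the effect.

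**The concern.** The PedsQL effect is the denominator of the headline ratio. An analyst following the text could compute a difference in change or a difference at 8 months. In any one sample these two differ by exactly the baseline difference between the arms, so the ICER depends on which is chosen.

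Whichever is chosen, the baseline score is either subtracted in full or not used at all. A regression weights it by its actual relation to the 8-month score, which removes the chance imbalance and gives a smaller standard error. The diagnosis stratum is in the planned regressions, but no section says that their arm estimate goes into the ICER. At stake are the reproducibility and precision of the main economic result, in a trial planned around 39 completers per arm.

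**Working it through.** **Inputs from the article.** Sample Size Calculation gives 39 completers per arm, 50% dropout and a target of 160. Check: 2 × 39 = 78, and 78 / 0.5 = 156. This agrees with 160 after rounding to 80 per arm. The 39 itself cannot be rebuilt, because no DIMS effect size or SD is given, and it was set for DIMS, not PedsQL. I use it only as the expected number per arm.

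**Assumptions.** The article gives no PedsQL SD and no baseline-to-8-month correlation r. I take equal variances at both times and r from 0.5 to 0.7.

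**Step 1: size of chance imbalance.** The SE of the baseline difference between arms is √(2/39) = 0.226 SD, so its 95% range is about ±1.96 × 0.226 = ±0.44 SD.

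**Step 2: how imbalance enters each estimate.** Per unit of baseline difference, the 8-month difference carries r, the difference in change carries r − 1, and the baseline-adjusted difference carries 0. A simulation of 20,000 trials (39 per arm, r = 0.6) gave slopes of 0.601, −0.399 and 0.003.

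**Step 3: precision.** Relative to the variance of the 8-month difference (set to 1), change has 2(1 − r) and the adjusted difference has 1 − r². The ratio of adjusted to change is (1 − r²) / [2(1 − r)] = (1 + r)/2.

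| r | SE, 8-month | SE, change | SE, adjusted | Variance cut v change | Variance cut v 8-month |
|---|---|---|---|---|---|
| 0.5 | 0.226 | 0.226 | 0.196 | 25% | 25% |
| 0.6 | 0.226 | 0.202 | 0.181 | 20% | 36% |
| 0.7 | 0.226 | 0.175 | 0.162 | 15% | 49% |

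(SEs in SD units, for example 0.226 × √0.75 = 0.196.) The simulated SEs at r = 0.6 were 0.226, 0.202 and 0.183. The small excess over 0.181 is the price of estimating the slope.

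At r = 0.6, adjustment is worth 39 / 0.80 ≈ 49 per arm against change, or 39 / 0.64 ≈ 61 per arm against the 8-month difference.

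**Step 4: illustration on the ICER, all values assumed.** Take SD 15, true effect 5 points, cost difference $100, r = 0.6, and a one-SE imbalance against BNBD-NDD of 0.226 × 15 = 3.4 points.

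- 8-month difference: 5 − 0.6 × 3.4 = 2.96 points, or 100 / 2.96 ≈ $34 per point.
- Difference in change: 5 + 0.4 × 3.4 = 6.36 points, or 100 / 6.36 ≈ $16 per point.
- No imbalance: 100 / 5 = $20 per point.

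The two readings differ by 6.36 − 2.96 = 3.4 points, the imbalance itself. The illustration sets all other sampling error to zero. The adjusted estimate would still have an SE of about 0.8 × 3.4 = 2.7 points, so a one-SE range of 2.3 to 7.7 points, or about $43 to $13 per point.

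**The case against.** **The wordings fit one quantity.** A reader might infer that the article defines the effect in three conflicting ways. It does not. The abstract's language of gain, and the Time Horizon statement about which assessments are used, let the other three sections be read together as a between-arm difference in change. This stands. What is left is ambiguity, because the 8-month difference is never ruled out.

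**Baseline is not ignored on that reading.** A change score uses baseline by subtraction. This also stands, and it means that the smaller gain, 15% to 25% of variance, is the relevant one. The 49% and the 61 per arm apply only to the 8-month reading. But subtraction is not adjustment: imbalance still enters with weight r − 1.

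**The regressions may be meant to supply the effect.** A reader might infer that they are separate from the ICER. The Overview does not say so. It places them directly after the sentence on the reference case and promises a group difference from each. It does not link them to the ICER either, and the listed covariates omit baseline PedsQL.

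**Model detail belongs in an analysis plan.** This is fair for a condensed article, and it is why the point is an improvement and not an error. Still, the article does commit to an ICER rule and a named covariate list, so a change to those statements can properly be suggested.

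**The dollar example proves little about this trial.** Agreed. Every input is assumed, and the ICER stays unstable after adjustment, as the $13 to $43 range shows.

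**Conclusion.** The point holds as a clarification and a gain in precision. The ICER effect is stated without a time contrast or model in the section that defines it. The likeliest reading is a difference in change, an 8-month difference remains possible, and neither is regression-adjusted for baseline PedsQL.

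On the likelier reading, adjustment lowers the variance of the effect by about 25% (r = 0.5) to 15% (r = 0.7). On the 8-month reading the figures are 25% to 49%. The formulas require only similar variances at the two times; the percentages rest on the assumed r, and the dollar amounts on further assumptions.

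A reader might infer systematic bias. The documents do not support that: under randomisation both contrasts are unbiased on average. Heavy dropout with a completers-only analysis could add imbalance that is not due to chance, but the article gives no figures by arm, and that is a separate matter.

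**What to change.** In Reference Case CEA, state that the effect in the ICER is the arm coefficient from a linear regression of 8-month PedsQL total on arm, baseline PedsQL total and NDD diagnosis stratum. Use the same definition in Outcomes for Economic Evaluation and in the Overview. The other covariates named in the Overview can remain optional. Show the raw baseline and 8-month means by arm as description only. The ICERs over the price range in Sensitivity Analysis should then use the same denominator.

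The cost is a few sentences and one regression. With four diagnoses the model has 6 parameters (intercept, arm, baseline, three diagnosis terms), leaving 78 − 6 = 72 residual degrees of freedom at the planned number of completers. No new data are needed: baseline PedsQL is already collected, and Missing Data already restricts the analysis to participants with both assessments. The Results section says that the economic data are being prepared for analysis, so the definition should be recorded and dated before any PedsQL comparison by arm is run.

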#### Secondary CCA

The CCA will assess the impacts on children’s sleep disturbance severity, parents’ daytime functioning, and psychosocial health. It adopts a broader perspective, providing a wider range of relevant costs and outcomes [24]. This allows various decision makers to focus on aspects and contexts specific to them [24]. The costs examined will extend beyond the family and include the costs of reported publicly and privately funded services sought.

